## Abstract

**Background:**

Early and intensive intervention is crucial for children with cerebral palsy (CP), particularly during the period when gross motor activities typically develop. Despite the prevalence of CP, robust evidence for effective early mobility interventions remains limited. Frame Running, which enables children with limited walking ability to engage in dynamic, high-intensity activities, has emerged as a promising approach, yet research on its effect in young children is currently lacking. The aim of this study is to implement and evaluate the effects of a mobility-focused training program combining Frame Running and goal-directed gross motor training, on mobility in every day life and cardiovascular health in children aged 2–5 years with CP.

**Method:**

The study uses a prospective repeated-measures intervention design with assessments conducted during baseline, intervention, and post-intervention follow-up phases. At least 18 children meeting the inclusion criteria (CP diagnosis, age 2–5 years, GMFCS II–IV) will participate. The design consists of three baseline measurements, a 12-week intervention phase and three post-intervention measurements, across approximately 5–6 months. The program combines home-based training and hospital-based group training, with parents as active trainers and therapists providing coaching. Frame Running and goal-directed training are tailored to individual goals, set collaboratively with families. Outcome measures include the Gross Motor Function Measure (GMFM-66), Functional Mobility Scale (FMS), Paediatric Evaluation of Disability Inventory Computerised Assessment Test (PEDI-CAT), time-based mobility tests: ultrasound assessment of muscle size and morphology, gait analysis, accelerometry (7-day activity monitoring), heart rate monitoring during training, and Goal Attainment Scaling (GAS). Feasibility and fidelity will be investigated by questionnaires.

**Discussion:**

By evaluating the Full Speed Ahead program, this study aims to improve understanding of how an early intensive family-centered mobility intervention may influence developmental trajectories and health in children with CP. If effective, the findings will have significant implications for planning both short- and long-term treatment and services for young children with CP. The prospective repeated-measures intervention design allows for both group-level and individual-level analysis of changes over time, thereby strengthening the evidence base for early, intensive, family-centered mobility interventions.

**Trial registration:**

ClinicalTrial.gov NCTO7374432, Registered November 18 2025.

## Background

Cerebral palsy (CP) results from a spectrum of early-acquired lesions affecting the developing brain. These brain abnormalities or injuries occur at varying time-periods during pregnancy or the neonatal period [1]. Such insults can lead to CP and are associated with a spectrum of functional limitations, which frequently manifest as restrictions in physical activities and participation in daily life, an issue that can be observed even in young children. A child’s ability to play, be physically active, and initiate independent mobility extends beyond simply reaching for a toy or getting to a destination. These abilities are crucial for environmental exploration, which underpins learning and supports physical, social, emotional, and cognitive development [2]. According to the the World Health Organization (WHO), young children should be engaged in at least 60 min of moderate-to-vigorous physical activity every day, while simultaneously minimizing sedentary behaviour, to promote optimal health and developmental outcomes [3]. This highlights the importance of providing even young children with CP opportunities to maximize their abilities, encouraging them to engage in high-intensity physical activity and initiate independent mobility to support health from an early age.

An estimated 17 million people currently live with CP (https://worldcpday.org). A significant proportion of individuals with CP experience reduced walking ability. The Gross Motor Function Classification System (GMFCS) categorizes children into five functional levels: children at GMFCS levels I and II walk independently but may have limitations in speed and coordination, while those at levels III to V typically require assistive technology for mobility. In high-income countries, 25% to 40% of children are classified within GMFCS levels III and IV, indicating substantial restrictions in physical activity [4].

Despite the substantial global population of individuals with CP, there remains lack of robust evidence supporting effective early mobility interventions that leverage the therapeutic window provided by rapid brain development and neuroplasticity in early childhood [5]. Yet, it is known that gross motor activities develop rapidly during the first years of life: children at GMFCS levels III and IV typically achieve about 90% of their gross motor potential by three years of age, while those at levels I and II continue to develop gross motor activities for a few more years [6, 7]. This underscores the critical importance of early intervention during the period of typical developmental progression, when the brain and central nervous system are most sensitive and adaptable [8].

It is also known that non-ambulant children are at the highest risk of developing musculoskeletal pathology, especially hip displacement, skeletal muscle contractures, joint deformity, and pain [9]. For example, reduced skeletal muscle volume is evident as early as 9 months of age [10]. Early intervention for this group of children at a young age, aiming to promote gross motor activities, is likely most effective prior to the development of skeletal muscle contractures, typically observed from 0 to 4 years of age. Therefore, evidence based early intervention programs are warranted.

### Evidence for early mobility training

To date, no studies have specifically targeted interventions aimed at increasing the daily dose of intense physical activity to improve health outcomes in children with CP, two to five years of age. Nevertheless, the literature indicates that early, intensive, and task-oriented mobility interventions can enhance gross motor outcomes in children with CP, especially when these interventions are integrated into daily routines [11, 12]. The implementation of accessible, family-centred programmes is crucial for optimising developmental progress, fostering independence, and promoting social participation [13].

Mobility devices play a pivotal role for children classified at GMFCS levels III–V. Evidence suggests that the provision of appropriate postural and mobility devices can improve emotional well-being, facilitate social interaction, support independent mobility, and reduce caregiver burden [14–16]. Walkers and gait trainers have been identified as valuable tools for supporting upright mobility, facilitating independence, and enabling social interaction with peers [17–19].

A range of mobility aids can support early self-initiated mobility in young children, including adaptive ride-on cars, partial body weight support systems, walkers and gait trainers, orthoses, assisting devices for crawling, and manual or powered mobility devices (Cheng et al. 2025). The process of acquiring and implementing these aids is multifaceted, encompassing initial assessment and prescription, device delivery and fitting, as well as thorough education for both caregivers and children. The expertise of clinicians and service providers is crucial for enable successful treatment, which affect both accessibility and outcomes. However, ongoing challenges—such as restricted access to devices, financial limitations, and inadequate training for families—must be addressed to ensure equitable provision and to optimise developmental outcomes [20].

In this context, Frame Running, previously known as RaceRunning, emerges as a promising addition to the range of mobility aids available for children with CP. This activity enables children with limited walking ability to engage in dynamic, high-intensity activity while promoting social participation and enjoyment. Despite its growing popularity, research on Frame Running remains scarce, even among older children [19]. Further studies are therefore needed to explore the potential of Frame Running as an early intervention to enhance daily physical activity, participation, and overall health outcomes in young children with CP.

### Importance of physical activity

Frame Running is a para-sport originally developed for athletes with moderate to severe difficulties in walking and/or running, but it is now increasingly utilised by children with CP [19]. It is one of the few options that enables physical activity at moderate to high intensity for this population. We have previously shown that regular participation in Frame Running positively influences skeletal muscle growth and cardiorespiratory function. Through Frame Running, children of all ages are able to actively engage and strengthen their musculature and stamina, thereby supporting improvements in both mobility and overall functional ability and cardiovascular health [21].

One of the principal physical benefits of Frame Running is the increased use of the skeletal muscles in the lower limbs. In typically developing children, it is evident that various forms of physical activity require distinct physical capacities [22, 23]. For instance, sprinting demands the development of strong muscles capable of producing rapid, forceful movements (i.e. high power), whereas distance running is more dependent on skeletal muscle endurance and robust cardiorespiratory fitness [23]. The maturation of these abilities is intrinsically linked to the processes of skeletal muscle growth and the way movement is practised throughout childhood. In children with CP, however, the scenario is considerably more complex. Although the underlying brain injury is non-progressive, the musculoskeletal system is gradually influenced by the child’s movement patterns and muscle use [24, 25]. Many children with CP encounter challenges in being sufficiently physically active, which can result in smaller and weaker skeletal muscles when compared to their typically developing peers. Additionally, joint mobility typically decline early in life, with fixed contractures—characterised by stiff and shortened muscles and tendons—frequently developing over time [25].

Current research exploring the determinants of movement ability in children with CP remains limited. Existing studies suggest that factors such as impaired selective motor control, disturbances of perception, reduced muscle strength, spasticity, restricted knee joint range of motion, and poor trunk control may all contribute to difficulties in efficient movement or running speed. However, the interplay between these factors and their relative contributions to overall physical capacity have yet to be fully elucidated. Moreover, other elements—including skeletal muscle mass and the extent of subcutaneous fat, which may influence the body’s capacity for physical work—have seldom been investigated in this population.

These considerations underscore the necessity of providing children with CP with tailored support and adaptive training regimes to promote sustained physical activity. In the absence of regular mobility and strengthening training, children are at increased risk of developing progressive functional limitations over time, potentially compromising both their health and independence.

### Framework for the *Full Speed Ahead* program

The *Full Speed Ahead (FSA)* program is designed for children with CP aged 2–5 years (GMFCS levels II–IV) and their families. The program is grounded in the *F-words* framework developed by Rosenbaum and Gorter [26], which comprises six key concepts—Function, Family, Fitness, Fun, Friends, and Future. This framework emphasizes a strengths-based perspective that focuses on what children *can* do rather than on their limitations. Collectively, these elements promote a holistic and empowering approach that supports improvements in physical health, motor function, and social-emotional development, while also fostering family engagement, peer interaction, and a positive outlook on future participation. A collaborative, family-centered approach underpins the intervention, emphasizing partnership, trust, and shared decision-making between professionals and families. This approach includes mutual goal setting, information exchange, and consistent support aligned with family priorities [13, 27, 28].

A central principle of the FSA program is repetition and massed practice, as skill acquisition is strongly dependent on the amount and quality of practice [29]. Children with typical development, for example, acquire walking skills through countless repetitions of standing, stepping, falling, and retrying, gradually enhancing balance, coordination, and strength [30–32]. Research also show that toddlers take up to 15,000 steps per day as they progress toward independent walking [30]. This developmental process occurs naturally through abundant practice opportunities in enriched, socially interactive environments rather than through explicit instruction. In alignment with this understanding, the present intervention aims to provide an enriched environment that promotes both motor development and social engagement [12].

The intervention consists of two primary components: Frame Running training and goal-directed gross motor training, offering complementary forms of practice. Frame Running aims to enhance mobility, health, and participation among children with CP. It provides an opportunity for children to experience the sensation of speed and movement, experiences that may otherwise be inaccessible due to mobility limitations, while engaging in physical activity that is both enjoyable and health-promoting [33]. This activity fosters enjoyment and a sense of achievement, while simultaneously enhancing cardiovascular fitness and overall well-being. Goal-directed gross motor training supports the acquisition of meaningful everyday activities, including maintaining and changing postures, sitting, standing, and mobility transposed into play in a rich environment [11, 12]. In accordance with family-centered practice, parents identify training goals based on each child’s strengths, priorities, and daily contexts [34]. The goal should be SMART: Specific, Measurable, Attainable, Relevant and Time-bound. They play an important role in engaging children to practice. While SMART formulations and structured scaling can support clarity and follow-up, an overly narrow focus on specific and time-bound targets may also have unintended negative effects, such as perceptions of failure and stress [35]. To reduce these risks, goal setting and scaling will be undertaken collaboratively with families, emphasizing strengths and realistic expectations during the intervention period.

The learning process will be facilitated by using the Goal Attainment Scaling (GAS), a five graded scale where each step will be well-defined and possible to evaluate [36].

To promote sufficient intensity and practice dosage, training is implemented across two complementary settings: home-based training and hospital-based group sessions. Parents play an active and central role in both contexts. During group sessions, trainers integrate all elements of the F-words framework—fostering social relationships, enhancing fitness, promoting enjoyment, engaging families, and cultivating optimism for future participation [26]. Group-based activities also enable children and families to learn from peers and experience the motivational benefits of social interaction, which enhances engagement and supports the long-term sustainability of physical activity participation. Although the intensity achieved through this combined approach can be questioned, it is supported by previous studies using similar designs [37, 38]. There is also evidence that, when appropriately supported, parents can deliver high-frequency, intensive training in the child’s natural environment, consistent with the principles of family-centered practice [39, 40]. Overall, this approach requires a substantial commitment from families, particularly given the young age of the children. However, embedding training within everyday routines is expected to facilitate a high number of repetitions and thereby provide an intensity of practice sufficient to effect the motor outcomes.

Coaching and collaboration with parents will have a prominent role in the FSA program. Coaching has a long established tradition in many early learning programs for children with disability [41, 42] and there are some moderate evidence for improving motor outcome in children with CP when a motor learning approach is used [43]. There is no generally accepted definition of coaching, only various definitions ranging from relationship-directed to intervener-directed concepts without a clear distinction between the instructing and coaching of parents [41]. In this study, the trainer will both act as a coach and supervisor for the parents, using an intervention-directed approach. Trainers are expected to be creative, engaging, and responsive to the children’s cues to maintain motivation and enjoyment, providing positive reinforcement throughout the sessions. They will also use structured coaching strategies, especially important for goal-directed gross motor training – such as modelling and demonstration, brief instruction, guided practice when needed, prompting and fading and immediate feedback linked to goal criteria – to support parents in progressing the child toward the pre-set goals.

## Methods

### Ethics and dissemination

Full ethical approval for this study has been obtained from the Swedish Ethical Review Authority (Dnr 2024-05809-01). All parents will receive both oral and written information about the study before signing an informed consent form. Data will be managed in accordance with regulations from the Karolinska University Hospital, including data de-identification, confidentiality and security. The principal investigators (PIs) will be ultimately responsible for communication of any significant protocol changes to the funder, Swedish Ethical Review Authority and study participants in a timely manner. A trial registration is available: ClinicalTrials.gov Identifier 2024-05809-01, Registered November 18 2025. Final study results will be presented at national and international meetings and published in peer-reviewed international journals.

### Hypothesis, primary and secondary objectives

The hypothesis is that mobility performance (e.g., distance, speed, or task-specific scores) will improve during the intervention phase and remain stable or continue to improve during the post-intervention follow-up period.(Fig. 1) Furthermore, we hypothesize that the heart rate–raising activities will lead to improved cardiovascular fitness and skeletal muscle development. The assessments chosen are based on these objectives.

**Fig. 1 Fig1:**
[figure not shown]
Timeline for the Full Speed Ahead program with prospective repeated-measures intervention design Baseline, and Post intervention

The primary objective is to improve the children’s mobility, with or without assistive devices, through a combination of Frame Running and goal directed gross motor training. The secondary objective is to increase their overall physical activity level through Frame Running.

### The study setting

Astrid Lindgren Children’s Hospital, a tertiary hospital in Stockholm, Sweden.

### Trial design

The study uses a prospective repeated-measures intervention design with assessments conducted during baseline, intervention, and post-intervention follow-up phases. There will be three baseline measurements, a 12-week intervention phase, and three post-intervention measurements (Fig. 1 and Table 1). Primary clinical outcomes are assessed during the baseline and follow-up phases, while process-related measures, see Table 1. The total study period is approximately 5–6 months.

**Table 1 Tab1:** Assessments to be collected during the training period, B=Baseline, F=Follow up

Assessments	B1	B2	B3	F1	F2	F3
GMFM-66	X	X	X	X	X	X
Funtional Mobility Scale	X	X	X	X	X	X
Time Up and Go	X	X	X	X	X	X
pROM and tonus/MAS		X		X		
Walking/running, 10 m	X	X	X	X	X	X
Frame Running 30 m	X	X	X	X	X	X
Ultra sound	X		X	X		
Gait analysis		X		X		
Pedi-cat, mobility	X	X	X	X	X	X
Prime P/SP	X		X	X		
Accelerometry	X		X	X		X
Goa Attainment Scale			X	X		X
Parent Evaluation						X

This design is informed by principles from single-subject research designs, particularly the use of repeated baseline measurements to characterize within-participant variability before the intervention. However, we do not expect children to return to baseline when the intervention is withdrawn. The planned sample size of at least 18 participants allows also for both individual-level and group-level analyses. This is an advantage when working with heterogeneous populations, such as children with CP, where variability in the magnitude and direction of response to treatment may obscure results in randomized controlled trials (RCTs) [44]. Repeated measurements across phases also allow exploration of individual response patterns and to investigate whether participant characteristics are associated with differential responses to the intervention. Although participants and therapists cannot be blinded to the intervention, outcome assessments are conducted by independent assessors with no involvement in the training phase.

### Recruitment of participants

Children will be recruited through the Astrid Lindgren Children’s Hospital and in collaboration with local habilitation services in Stockholm, Sweden. Eligible participants must meet the following inclusion criteria: a diagnosis of cerebral palsy; age 2–5 years; GMFCS level II–IV; medically stable conditions; and sufficient cognitive ability to benefit from group sessions and follow simple instructions. Both parents and children must have adequate proficiency in Swedish or English as these language skills are essential for participation in data collection and group training. Additionally, families must be able to transport the Frame Runner to training sessions.

Parents of eligible children will first receive verbal information about the study from a senior therapist who is not involved in the child´s regular treatment. Written information will subsequently be provided. Families will then have the opportunity to discuss the study in detail with the investigators before giving informed consent. Families who do not wish to participate will continue to receive usual care through their habilitation services. Eligible families will be identified by clinical staff until the target sample size is reached. This constitutes a convenience sample.

### Statistical method

Demographic and clinical characteristics of the participating children and parents will be summarized using descriptive statistics. Continuous variables will be presented as means and standard deviations or medians and interquartile ranges, as appropriate, while categorical variables will be presented as frequencies and percentages.

Outcome data will be analyzed at both the individual and group levels. At the individual level, graphical displays will be used to visualize changes over time for each participant across study phases. Visual inspection will focus on changes in level, trend, and variability between baseline and follow-up measurements. These graphical analyses will be used to complement the quantitative analyses and to explore individual response patterns. At the group level, outcome measures obtained at baseline and post-intervention follow-up will be compared using appropriate repeated-measures statistical methods. Depending on the distribution and characteristics of the data, analyses may include paired t-tests or non-parametric alternatives such as the Wilcoxon signed-rank test. Effect sizes (e.g., Cohen’s d or equivalent non-parametric effect size measures) will be calculated and reported to facilitate interpretation of the magnitude of change. Given the limited number of observations within each phase, formal assessment of autocorrelation is not expected to provide reliable estimates. Results will therefore be interpreted with consideration of the dependency inherent in repeated measurements obtained from the same participant and in conjunction with graphical inspection of individual trajectories. In cases where graphical and statistical findings diverge, results will be interpreted cautiously.

Missing data will be described for each outcome measure and study phase. The number and proportion of missing observations will be reported together with reasons for missingness when available. Given the limited number of repeated measurements within each phase, missing values will not be imputed. Analyses will be based on available data, and the potential impact of missing observations on the interpretation of findings will be considered when reporting the results. Participant withdrawal and missed assessments will be reported separately.

To ensure for not blinded assessors of GMFM, we have incorporated independent, blinded secondary scoring for a random subset of 20% of the video recordings. Inter-rater reliability (IRR) will be formally assessed using Cohen’s Kappa / ICC. To proactively mitigate bias, if the initial IRR coefficients fall below [e.g., 0.80], a fully blinded primary assessor will be utilized to re-score the entire dataset.

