## Discussion

The FSA program aims to address the need for effective interventions targeting gross motor function and health in young children with CP. Currently, there is a lack of evidence for effective training programs for this group of children [11, 64]. In particular, research evaluating interventions for non-ambulant children with CP is scarce; most existing studies have focused on children classified as GMFCS levels I to III, leaving those at levels IV and V underrepresented and often without access to evidence-based interventions [65].

By implementing a new early and intensive program, consisting of a combination of Frame Running and goal-directed training, the FSA program aims to facilitate higher levels of functioning and participation than would be expected without such intervention, both short and long term. If proven effective, this approach could have substantial implications for planning both short- and long-term treatment and support services for young children with CP.

The prospective repeated-measures intervention design allows detailed analysis of individual response patterns over time, while also supporting group-level analyses. This is an advantage, as the variation among children is considerable and prospective repeated-measures intervention design allows for a broad understanding of the intervention impact on each participant, supporting the development of more effective and personalized treatment strategies for children with CP.

This study has limitations. The prospective repeated-measures intervention design does not include randomization or a control group, which limits causal inference. Blinding is also limited, as participants and therapists cannot be blinded to the intervention, although independent assessors will perform outcome assessments whenever possible. In addition, the relatively small sample size and the heterogeneity of children with CP may limit generalizability. Variation in adherence to home-based training may also affect outcomes. However, repeated assessments across study phases and the combination of individual- and group-level analyses are expected to provide important information about the feasibility and potential effects of the intervention.

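### Individual change is judged only by eye from at most three points per phase, without the baseline variability as a yardstick, so noise or ordinary development can be read as individual response

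*Protocol article*

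**What the plan says.** The protocol article's Statistical method section describes the individual-level analysis as graphical: "At the individual level, graphical displays will be used to visualize changes over time for each participant across study phases". It then names what is looked at: "Visual inspection will focus on changes in level, trend, and variability between baseline and follow-up measurements". The role of the graphs is stated too: "These graphical analyses will be used to complement the quantitative analyses and to explore individual response patterns". The section gives no numerical criterion for a single child.

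The Trial design section says the design borrows from single-subject research, "particularly the use of repeated baseline measurements to characterize within-participant variability before the intervention". It presents individual-level analysis as an advantage in a heterogeneous population. It also plans to examine whether characteristics of the children go with differing response. The Discussion says the design "allows for a broad understanding of the intervention impact on each participant" and links this to personalised treatment strategies.

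In Table 1, six of the 13 rows are measured at all three baselines and all three follow-ups: GMFM-66 (primary), Functional Mobility Scale, Timed Up and Go, 10 m walk/run, 30 m Frame Running and PEDI-CAT mobility. The other rows have fewer points.

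**The concern.** The stated reason for measuring three times before training is to learn how much a child's score varies without it. The analysis looks at that variability on a graph but never turns it into a yardstick for a child's change. Two things other than the intervention can lift the follow-up points: measurement noise and ordinary development. The Background says gross motor ability is still developing at these ages, to a degree that depends on GMFCS level, and the Discussion concedes that there is no control group.

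At stake is how statements about single children are read, and the planned look at which characteristics go with response. The rule that diverging graphical and statistical findings be interpreted cautiously gives little protection here. Development moves the graphs and a paired baseline-to-follow-up test in the same direction, so the two need not diverge.

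**Working it through.** The plan gives no figure to reproduce: it states no within-child SD, growth rate, significance level or power.

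**Inputs from the article**
- 3 baseline and 3 follow-up visits, with a 12-week intervention (Trial design, Table 1).
- At least 18 children (Sample size).
- Study length: "The total study period is approximately 5–6 months" (Trial design).

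**Assumptions**
- Independent visit noise with SD s_w, equal across children.
- Even spacing of d weeks within each phase. Fig. 1 is not shown, so d = 2, 3 and 4 are used, with 3 as the central value.
- Linear development of 0, 0.05 or 0.10 s_w per week. The article gives no rate, so the range starts at zero.

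**1. How often noise alone looks like a clear shift.** As an example of a pattern that looks convincing, take all three follow-ups above all three baselines.
- With no drift, all orderings are equally likely: 3!·3!/6! = 1/20 = 5% per child.
- Expected in 18 children: 18 × 0.05 = 0.9.
- At least one of 18, per outcome: 1 − 0.95^18 = 60%.

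**2. The same pattern with development and no treatment effect.** In 400,000 simulated children at 3-week spacing, it occurs in 22.6% at 0.05 s_w per week and 52.2% at 0.10 s_w per week. That is about 4 and 9 of 18. The full range from zero drift is 5–52%.

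**3. Single-child trend.** The phase centres are 12 + 2d weeks apart, and the sum of squared baseline times is 2d². The standard error of the follow-up mean minus the child's own projected baseline line is s_w × sqrt(1/3 + 1/3 + (12 + 2d)²/(2d²)).

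| d (weeks) | gap (weeks) | 2d² | SE |
|---|---|---|---|
| 2 | 16 | 8 | 5.7 s_w |
| 3 | 18 | 18 | 4.3 s_w |
| 4 | 20 | 32 | 3.6 s_w |

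**4. What B1–B3 can supply.** The limit for mean(F1–F3) − mean(B1–B3) is t × s_w × sqrt(1/3 + 1/3).
- From one child's own baselines (2 df): 4.303 × 0.816 = 3.51 s_w. The SD itself then has a 95% interval from 0.52 to 6.28 times its estimate, which is too loose to use.
- Pooled over 18 children (18 × 2 = 36 df): 2.028 × 0.816 = 1.66 s_w. Expected beyond it in the direction of improvement from noise alone: 0.025 × 18 = 0.45 children.

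**5. What that limit does not do.** With spacing of 2.5–3.5 weeks and no treatment effect, the 1.66 s_w limit still flags 20–24% of children at growth of 0.25 s_w per month and 64–74% at 0.5 s_w per month.

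**6. Subtracting the cohort's baseline slope.** At d = 3 the projected mean slope of 18 children has standard error 18/sqrt(18 × 18) = 1.0 s_w. The adjusted change has SD sqrt(0.667 + 1.0) = 1.29 s_w, and its limit is 2.028 × 1.29 = 2.6 s_w. Keeping 1.66 s_w for the adjusted change would flag about 10% by chance (1.66/1.29 = 1.29 standard deviations), or about 1.8 of 18. The slope error is common to all children, so it moves them together.

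**The case against.** The best reply is that the graphs are a modest, declared exploration. The article calls them complementary, includes trend and variability among the features inspected, admits that there are few observations per phase and concedes that causal inference is limited. Visual inspection is also usual in the single-subject tradition that the design draws on, and a per-child limit could sit in an analysis plan that is not shown.

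Most of that stands as a limit on how strongly the point may be put. A reader might infer that children will be classed as responders or non-responders. The article never says so, and the planned look at characteristics is equally compatible with a continuous change score. A reader might also take complete separation of the six points to be the protocol's criterion. It is not; it serves here only to show what chance can produce. The drift rates have no source in the article, and the Background says that children at GMFCS levels III and IV reach about 90% of their gross motor potential by age three, so drift may be small in much of the sample.

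The reply does not remove the point. The individual-level method is stated, not left open. The stated purpose of the repeated baselines is not carried into any calculation. The Trial design and Discussion sections ask more of the individual results than unaided inspection of three points per phase can give.

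**Conclusion.** The point holds as a weakness in a stated method: individual change is judged without a noise yardstick, though pooled baseline data could supply one. Noise or development can, not will, be read as response. The share of children showing an apparently clear shift with no treatment effect runs from 5% (no drift) to about 52% (0.10 s_w per week), under independent noise and 3-week spacing. The uninformative single-child trend does not depend on any drift rate: its standard error is 3.6–5.7 s_w for spacing of 4 to 2 weeks.

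It would be wrong to conclude that B1–B3 solve the whole problem. They give a usable noise level only when pooled, and a noise limit does not separate development from intervention response. The group-level comparison is not affected by this point. The change is worth making because it is cheap and puts the repeated baselines to their stated use.

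**What to change.** Keep the graphs, described as descriptive, and add to the Statistical method section:

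- For outcomes measured at all six visits and analysed on a numerical scale, estimate s_w by pooling the within-child B1–B3 variance. Compute each child's unadjusted change, mean(F1–F3) − mean(B1–B3), and compare it with t × s_w × sqrt(2/3), which is 1.66 s_w with 18 complete children.
- Report the number of children beyond the limit beside the number expected from noise alone, about 0.45 of 18 in the direction of improvement (a decrease for timed tests).
- If a change adjusted for the cohort baseline slope is also shown, give it its own limit that includes the slope error, about 2.6 s_w at 3-week spacing. Note that this error is shared by all children and that one slope may not fit all GMFCS levels.
- Do not interpret trend change for single children.
- Use the continuous change score when relating characteristics to response.
- State that change beyond noise does not separate intervention response from development.

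The cost is a few sentences and no new data. The downsides are that fewer children will be described as changed, and that pooling assumes similar noise across a heterogeneous group.
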